### Interventions

All the study subjects will be given various postural recommendations.

True moxibustion (TM): The first intervention will be made at the Healthcare Clinic. This session (overseen by the midwife responsible) will serve as a training session for the friend or relative who is to apply the remaining sessions, at home. The mother should lie down, face up, wearing comfortable clothing and with no pressure at the waist from buttons, belt, etc. and with her legs slightly bent at the knee. Heat will be applied for 20 minutes, by means of a moxa cone (herbal preparation with *Artemisia vulgaris*) at point BL67 (*Zhiyin*), close to the outer angle of the little toenail (Figure 1). The heat will be applied from a distance of 1.5–3 cm, to ensure that the subject notices a feeling of warmth in the zone, but without any pain or burning. The application site (right or left foot) will be alternated every 2 minutes or more often if any untoward sensation of heat is felt.

**Figure 1 F1:**
[figure not shown]
**Acupuncture points used**. Location of the two acupuncture points used in the study; Zhiyin BL67 for Group A and Yinbai SP1 for Group B.

False/Sham moxibustion (SM): This procedure will be identical to that applied to the TM group except that the point stimulated will be a non-active one – according to the principles of Traditional Chinese Medicine, point SP1 (*Yinbai*), close to the inner angle of the big toenail (Figure 1).

Control group, under observation (CG): The subjects in this group will receive the standard treatment, in accordance with the Andalusian Healthcare System Treatment Guide "*Embarazo, parto y puerperio*" (Pregnancy, birth and childcare) (2^nd ^edition).

### Outcome measures

#### Primary outcome

The rate of cephalic presentation at term will be taken as the primary endpoint variable.

#### Secondary outcomes

Secondary outcomes will include the rate of cephalic presentation at week 38 of gestation (CP38) (determined by echography) and the number of days of treatment received until version occurs. The intervention allocation to the moxibustion groups (true or sham) will be controlled by asking the subject: "What type of treatment do you think you received?" Three possible answers may be given: A) Real; B) Sham; C) I don't know. The following sociodemographic covariables will be recorded: age, race, educational level, occupation, level of income, occupational activity, weight (kg), height (cm). In addition, these obstetric-gynaecological variables will be recorded: gestational age when subject was included in the study, determined by foetal biometry; type of presentation, determined by echography (characterized as breech, oblique or transverse presentation); foetal biometry (biparietal diameter, abdominal diameter and length of femur) [week of gestation when biometry is performed]; location of the placenta (categorized as anterolateral or posterior), parity (number of previous births), and previous miscarriages. The following security variables (in the first session) will be used: maternal heartbeat prior to the stimulus; foetal heartbeat prior to the stimulus; maternal heartbeat at 5 minutes after the stimulus; foetal heartbeat at 5 minutes after the stimulus. The security variables determined during the treatment will be recorded on the self-reported questionnaire which is completed by the subjects after each home treatment session, with data on foetal movements, uterine contractions, maternal heartbeat and any other incident following the stimulation. Finally, a number of other variables related to the birth will be recorded, including gestational age at birth, weight of the neonate, sex of the neonate, type of birth (vaginal or caesarean section), and APGAR score at 1 and 5 minutes (Figure 2).

**Figure 2 F2:**
[figure not shown]
**Flow diagram for the study**. Work scheme with description of assessment visits and times.

### Data collection and analysis

#### Data collection

Most of the data obtained from the study will be recorded in the Pregnant Woman's Health Passport and in the Child's Health Passport. A Data Collection Record (DCR) form will be designed, including the variables of interest that will be noted down by the midwife collaborating with the healthcare clinic. We have designed a self-reported questionnaire for the subject to fill in after each session (during the two weeks' duration of the treatment), with data such as the number and intensity of foetal movements, the uterine contractions, maternal heartbeat and any relevant incidents that may have occurred following the stimulation. This information will be codified and sent weekly to a database for subsequent statistical analysis.

The baseline and intermediate evaluations, together with the results data obtained at birth, will be made by the corresponding midwife. The self-reported questionnaires will be oriented by the same evaluating personnel. Collateral effects and possible adverse reactions to the treatment will also be noted.

#### Statistical analysis

In the first place, we will perform an analysis following intention-to-treat principles, including all the subjects with valid data, irrespective of whether or not they received the treatment assigned. These results will be compared with those obtained by an on treatment analysis, in order to determine whether violations of the protocol led to bias. The subjects for whom deviations from the protocol are observed – such as not having received the complete treatment, or as having received insufficient follow up, will be excluded from the per treatment analysis. A comparison will be made of respondents and non-respondents to reveal the existence of any selection or classification bias.

Comparability between the interventions and usual care groups will be assessed at baseline to evaluate the differences. The magnitude of the difference in any imbalance produced by the random assignation to the groups will be evaluated using means and proportions ratios (using that of the usual care group as the reference level).

In the bivariate analysis of the magnitude of the association between exposure and effect, diverse tests of statistical significance will be employed to make comparisons between *k *samples (parametric or otherwise, depending on the asymmetric or otherwise distribution of the results variables and on the homogeneity of their variances), taking the usual care group as the reference level and using comparison tests for differences in proportions in the primary outcome measure.

For the primary outcome variable, logistic regression models will be created, using ITT analysis. These will include, firstly, the group variables (experimental vs control), taking the control group (usual care) as the reference level. Then, the model will be adjusted for the variables of age, parity and weeks of gestation at randomization (the baseline variables). Adjustment will also be made for other possible confounders (the variables that are imbalanced in the baseline analysis) using criteria of statistical significance (*P *< 0.05) and of confusion (change of over 10% according to the magnitude estimator – the incidence odds ratio). The detection of possible interactions with the "treatment group" variable will be carried out by means of statistical significance criteria for the corresponding terms of interaction, introducing the relevant additive and multiplicative interaction variables. The level of significance will be set at <0.05 α for the global comparisons, although this level will be penalized by the existence of an intermediate level, as explained below. A cost effectiveness analysis, from the standpoint of the Andalusian Public Healthcare System, will be performed.

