### Randomization and treatment allocation

The randomization of the three branches of the study will be carried out on a centralized basis, by a statistician who is otherwise unrelated to the study, using a 1:1:1 scheme in blocks of 12 and stratifying by clinics. There will be the same number of sets of envelopes as there are of participating midwives/clinics (some 40 midwives are expected to take part). Each set will contain 12 opaque envelopes which will be sealed after the introduction of a card with the letter corresponding to the allocation to the group as determined by the software-generated sequence: Group A (true moxibustion), Group B (sham moxibustion) and Group C (control). After the baseline assessment and the signing of informed consent, these sealed, opaque, numbered envelopes will be used in sequence to assign the study subjects to one of the three groups. The collaborating midwife will note on the card the pregnant woman number and that of the clinic. At the end of the study, the chief researcher will check each card against the original randomization list to confirm that all the subjects received the treatment that had been assigned to them. This method ensures that neither the clinics nor the healthcare professionals taking part in the study will be involved in the randomization process and thus will not be able to influence it. A patient may be withdrawn from the study at any time, at her discretion or that of the researcher. The reasons for this will be noted down on the summary page of the Data Collection Record (DCR). The midwives who participate in the study have attended a 10-hour training course on postural recommendations and moxibustion techniques, and in which criteria for data collection were standardised.

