### Sample size

The sample size has been predetermined at n = 492 patients, for a significance level of 95%, a power of 90% and a difference in the success rates of either of the intervention groups (A or B) with the control group (C) of 20%, assuming a dropout rate of 25%. These values were calculated using SamplePower version 2 software.

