## Discussion

As observed above, the problem identified by the analysts of the only Cochrane review available is the low methodological quality of most of the studies that have been made. In designing the present study, special care was taken regarding the characteristics conforming a quality RCT, in accordance with the recommendations made by Jadad [18]. Nevertheless, the following foreseeable limitations should be pointed out: firstly, the sample was extracted from the universe of pregnancies managed within the Andalusian Public Healthcare System (SSPA), and therefore the conclusions drawn will only be applicable to this population group. The complexity of including private clinics in the study led us to renounce this idea, especially in view of the fact that the coverage of the pregnancy control programme within the public system is almost universal; moreover, the pregnant women who make use of private systems do not stop receiving the follow-up attention scheduled under the public healthcare system. From the bibliographic review performed, neither does it seem that social class influences the incidence of breech presentation or its version during gestation. It is very likely, therefore, that the results obtained will resemble those that would be derived for the entire population of pregnant women in Andalusia. The inclusion of a routine control of the official programme (an echography performed in week 32) also avoids possible selection bias. Thus, with the involvement of the gynaecologist performing this examination, and of the midwife who participates in routine care, the uptake is ensured of 100% of the cases of NCP detected during the study period, while the rate of losses to follow up is minimised.

Secondly, there exists the possibility (which has actually occurred in other studies) of a pregnant woman refusing to take part when she discovers which branch of the research study she has been assigned to. This is applicable to the formation of the control group, as normally any intervention (whether true or sham moxibustion) will be willingly accepted by a pregnant woman in a situation of some risk. In the studies examined, this has actually occurred in only a very small percentage of cases, but note should be taken of this possible source of bias.

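### The analysis labelled intention-to-treat keeps only women with valid data while 25% dropout is allowed for, so loss related to outcome differently by arm could bias the primary comparison

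*Protocol article*

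**What the plan says.** Under Statistical analysis, the article states that the first analysis follows intention-to-treat principles, "including all the subjects with valid data, irrespective of whether or not they received the treatment assigned". The same section applies it to the main result: "For the primary outcome variable, logistic regression models will be created, using ITT analysis". The endpoint is fixed under Primary outcome: "The rate of cephalic presentation at term will be taken as the primary endpoint variable".

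Three other places bear on who might lack valid data:

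- Sample size: "The sample size has been predetermined at n = 492 patients", "assuming a dropout rate of 25" per cent.
- Randomization and treatment allocation: "A patient may be withdrawn from the study at any time, at her discretion or that of the researcher". Reasons are to be noted, but the text does not say whether outcome data are still collected afterwards.
- Discussion: the article foresees "a pregnant woman refusing to take part when she discovers which branch of the research study she has been assigned to". It ties this to the control group, reports that it was rare in the studies examined, and still flags it as a potential bias.

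The stated checks are a comparison of respondents with non-respondents and an on-treatment analysis. The logistic model is also adjusted for age, parity, gestational week and imbalanced baseline variables. Under Data collection, the midwife gathers the results at birth, and most data are recorded in routine Health Passports.

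**The concern.** Intention to treat has two parts: women stay in the arm to which they were allocated, and all randomised women are counted. The quoted rule secures the first and gives up the second. Any woman without a valid outcome leaves the primary comparison, whatever the reason.

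This matters more here than in a fully blinded trial. Women in the control arm know that they receive no moxibustion. The midwife who handles the allocation card also collects the data. A researcher may remove a woman from the study, not merely from treatment. Reasons for missing data can therefore differ between arms. If they are also linked to whether the foetus turned, the comparison loses the protection of randomisation.

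Neither stated check repairs this. Comparing respondents with non-respondents can reveal a problem but does not correct the estimate. The on-treatment analysis also drops women with insufficient follow-up, so agreement between the two analyses says nothing about missing outcomes.

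**Working it through.** **Inputs.** Total 492, 25% dropout, 90% power and a 20-point difference (Sample size); 1:1:1 allocation (Randomization and treatment allocation); 70% v 50% (Background). Two-sided 0.05 is assumed, because the article gives only "for a significance level of 95%, a power of 90" per cent.

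**Reproducing 492.** The two-proportion formula without continuity correction gives 124 per arm with pooled variance under the null and 121 unpooled. Divided by 0.75 and rounded up, these are 166 and 162 per arm, or 498 and 486 in total. Both are within 3% of 492. Exactly, 492 = 3 × 164 and 164 × 0.75 = 123. The design thus rests on 123 analysable women per arm and tolerates 492 × 0.25 = 123 randomised women outside the primary comparison. Power at 123 per arm is 89.8%, so the sample size is sound at 0.05 and loss of power is not the issue.

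**Bias formulas.** Let *p* be the true cephalic rate, *m* the share missing, *s* the cephalic rate among the missing, and *rc*, *rn* the retention of women with cephalic and non-cephalic outcomes. The complete-case rate is

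(p − m·s)/(1 − m), or equivalently p·rc/[p·rc + (1 − p)·rn].

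**No true effect, p = 0.50 in both arms.** All loss patterns below are assumptions; the article gives none.

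| Pattern | Observed rates | False difference |
|---|---|---|
| Retention 85% v 65%, unrelated to outcome | 50.0% v 50.0% | 0 |
| Retention 80/70% (cephalic/non-cephalic) in both arms | 53.3% v 53.3% | 0 |
| 5% lost in C, 65% of them cephalic; none lost in A | 50% v (0.5 − 0.05×0.65)/0.95 = 49.2% | 0.8 points |
| 10% lost in C, 65% of them cephalic; none lost in A | 50% v (0.5 − 0.10×0.65)/0.90 = 48.3% | 1.7 points |
| 25% lost in each arm, retention 80/70% v 75/75% | 0.40/0.75 = 53.3% v 50% | 3.3 points |
| 25% lost in each arm, retention 85/65% v 75/75% | 0.425/0.75 = 56.7% v 50% | 6.7 points |
| 25% lost in each arm, retention 90/60% v 75/75% | 0.45/0.75 = 60% v 50% | 10 points |
| 25% lost in each arm; the missing are 35% cephalic in A, 65% in C | (0.5 − 0.25×0.35)/0.75 = 55% v (0.5 − 0.25×0.65)/0.75 = 45% | 10 points |

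For the three retention rows with 25% loss and a non-zero difference, a two-sided 0.05 test on 123 per arm (normal approximation) has a type I error of about 8%, 18% and 35%.

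**Bounds.** Suppose 70% v 50% is observed and 25% are missing in each arm. Over all randomised women the difference could be as low as 0.75×0.70 − (0.75×0.50 + 0.25) = −10 points, or as high as (0.75×0.70 + 0.25) − 0.75×0.50 = +40 points. These are extremes, not forecasts.

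**The case against.** The other side has good points, and several stronger readings fail because of them.

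- **A quarter of outcomes will be missing.** A reader might infer this, but the article does not say it. The 25% is a planning allowance for dropout. It may include women who stop treatment but whose presentation at birth is known, and the rule keeps them. The Discussion also says that losses are kept to a minimum.
- **The plan predicts control-arm refusal.** It calls refusal a possibility that was rare elsewhere. Scenarios with heavy refusal in that arm have no support in the text; at 5% the bias is under 1 point.
- **Unequal dropout biases the result by itself.** It does not, as the first table row shows. Loss must also relate to outcome, or to predictors left out of the model, and differently by arm.
- **Women who deliver early leave the analysis.** This is an inference. The article does not say how births before term count, and women at risk of premature birth are excluded at entry.
- **The safeguards are ignored.** The covariate adjustment does deal with loss that depends only on arm and the adjusted variables. It does not deal with loss that depends on the outcome itself.
- **Missing-data methods belong in an analysis plan that is not shown.** Their absence from an article is indeed no finding. What the article does state is the analysis set, and that set is restricted to valid data.

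The mismatch between label and set therefore stands. The claim of a large bias does not.

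**Conclusion.** The concern holds in limited form. The document itself fixes a complete-case primary analysis under an intention-to-treat label, allows for up to 123 of 492 women to drop out, and corrects nothing if loss depends on outcome differently by arm. The comparison can be biased; nothing in the document shows that it will be.

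The size and direction are unknown. With no true effect, the assumed patterns run from under 1 point, through about 3 points with type I error near 8%, to about 10 points when selection is strong or opposite in the two arms. The planned effect is 20 points. These figures assume a 50% cephalic rate and loss patterns that the article neither gives nor rules out. If presentation at birth is in fact obtained for nearly every woman, the bias will be small.

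**What to change.** 1. Define the primary analysis set as all randomised women in their allocated arm.
2. Record presentation at birth with the delivery data that the midwife already collects, for every woman, including those who stop or are withdrawn from treatment, unless she withdraws consent to data use. The article does not say that presentation itself is entered in the Health Passports, so this should be confirmed.
3. State that withdrawal by the researcher ends treatment, not outcome collection. When treatment should stop is not at issue here.
4. Replace the complete-case-only result with imputation for outcomes still missing, and add a sensitivity analysis such as a tipping point.
5. State how births before term count towards the primary endpoint. The endpoint need not be redefined to any gestational age.

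The cost is revised wording, some retrieval of delivery records for women who stop attending, and modest extra analysis. It is best done before data accrue, because outcomes not collected cannot always be recovered later.

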Acupuncture and moxibustion are therapeutic techniques found in traditional Chinese medicine. They have been employed since ancient times, and specific recommendations in Chinese texts include the application of heat (moxibustion) by the combustion of *Artemisia vulgaris *(moxa) over an acupuncture point in order to correct NCP [12,13]. This latter point, known as *Zhiyin *(BL67) is located in the outer corner of the little toenail. In addition to moxibustion, acupuncture may also be used, either alone or in association with moxibustion, on this or other points, although it has been found that the highest level of effectiveness is associated with the application of moxibustion alone [14]. A Cochrane review [15] concluded that there is insufficient evidence from the studies included in its analysis, and observed that there have been few well-designed studies (only 3 are included in the review) and that most of them used a small sample. Some studies with a larger sample, such as that by Kanakura et al. [16], were not randomized. A larger, systematic review that we have carried out this year (manuscript submitted for publication), with the inclusion of new studies performed to date, and with the incorporation of those published in Chinese in the last 10 years, shows that studies contain to be of low methodological quality. We estimate a correction rate of 70% (versus 50% in control groups) among pregnant women treated with moxibustion. Among the studies carried out so far, no reports have been made of side effects, although the smoke generated while the moxa is burned may irritate the respiratory tracts. Nevertheless, there is no evidence to support this hypothesis [15]. Neri et al. [14,17] have made a cardiotocographic study of the effects of moxibustion on foetal heartbeat, and concluded that no harm is caused by this process.

The present study is funded by the Health Ministry of the Andalusian Regional Government (Project No. 0053/2007).

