### Research questions are

How effective is moxibustion at point BL67 in terms of the rate of full-term cephalic presentations?

How effective is moxibustion at point BL67 in terms of the rate of caesarean sections?

What is the effect of moxibustion at a non-specific point such as SP1 in pregnancies with NCP?

To what extent are the pregnant women to whom the study techniques are applied confident of the outcome?

How safe is the technique in terms of increased rates of changed foetal cardiac rhythm, the risk of premature birth, and changes in APGAR scores at 1 minute and at 5 minutes?

What is the cost-effectiveness of treatment with moxibustion for cases of NCP?

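### The fixed-covariate model is written for the primary outcome only; extending it to caesarean section and week-38 presentation would recover a little power at no cost

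*Protocol article*

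**What the plan says.** The Statistical analysis section of the protocol article describes two layers of comparison.

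- **Bivariate layer.** It is general in scope: "In the bivariate analysis of the magnitude of the association between exposure and effect, diverse tests of statistical significance will be employed". The tests compare k samples, parametric or not, with usual care as the reference. The primary outcome is then singled out for tests of proportions. No covariates enter.
- **Regression layer.** It opens with a restriction: "For the primary outcome variable, logistic regression models will be created, using ITT analysis". The first model holds treatment group only. The second adds maternal age, parity and gestational age at entry. Further confounders may join on significance and change-in-estimate criteria.

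No adjusted model is described for any other outcome. Yet the list of research questions includes "How effective is moxibustion at point BL67 in terms of the rate of caesarean sections". The Secondary outcomes section names cephalic presentation at week 38, and records type of birth, parity, age and gestational age at inclusion.

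**The concern.** The protocol judges three baseline variables worth fixing as covariates for cephalic presentation at term. It gives no reason to drop them for two closely related outcomes in the same women. Caesarean section carries much of the trial's clinical rationale in the Background, and under plausible rates it has less power than the primary endpoint. If parity predicts type of birth, a comparison that ignores it discards information already collected. A chance imbalance in parity would also be adjusted for in one answer and not in the other. At stake is some power on two supporting outcomes and consistency of presentation, not validity.

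**Working it through.** **1. Evaluable women per arm (Sample size section).** The stated inputs are "for a significance level of 95%, a power of 90" per cent, "a difference in the success rates of either of the intervention groups (A or B) with the control group (C) of 20" percentage points, and "assuming a dropout rate of 25" per cent. The Background supplies the rates: "We estimate a correction rate of 70% (versus 50% in control groups) among pregnant women treated with moxibustion". A two-sided test of 50% versus 70% at 0.05 with 90% power, without continuity correction, needs 124 per arm. Then 124/0.75 = 165.3, rounded up to 166, and 3 × 166 = 498 against the stated 492, a 1.2% difference. Backwards, 492/3 = 164 and 164 × 0.75 = 123 evaluable per arm, which gives 89.8% power. The stated size reproduces, and 123 is used below.

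**2. Assumed caesarean rates.** The document gives none. Assume 90% caesarean if non-cephalic and 22% if cephalic:
- control (50% cephalic): 0.50 × 0.90 + 0.50 × 0.22 = 0.560
- moxibustion (70% cephalic): 0.30 × 0.90 + 0.70 × 0.22 = 0.424
- difference: 0.136

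**3. Unadjusted power.** The variance sum is 0.560 × 0.440 + 0.424 × 0.576 = 0.4906. SE = √(0.4906/123) = 0.0632, z = 0.136/0.0632 = 2.153, and power = Φ(2.153 − 1.96) = 57.7%. With a pooled null variance it is 56.9%.

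**4. Power adjusted for parity.** Assume half the women are nulliparous and parity has odds ratio 2, 3 or 5 for caesarean section. Solve for the two parity-specific risks in each arm that average to 0.560 and 0.424. Replace each arm's variance p(1 − p) by the mean of its two within-parity variances.

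| Parity OR | Control risks | Moxibustion risks | Variance sum | SE ratio | z | Power | Gain (points) |
|---|---|---|---|---|---|---|---|
| 2 | 0.475, 0.645 | 0.340, 0.508 | 0.4765 | 0.985 | 2.185 | 58.9% | 1.2 |
| 3 | 0.428, 0.692 | 0.293, 0.555 | 0.4562 | 0.964 | 2.233 | 60.8% | 3.1 |
| 5 | 0.372, 0.748 | 0.238, 0.610 | 0.4208 | 0.926 | 2.325 | 64.2% | 6.6 |

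Simulating the logistic models themselves (4,000 runs per scenario) gave 55.8% to 57.3%, 57.1% to 60.4%, and 56.3% to 63.5%, so gains of 1.5, 3.3 and 7.2 points. Other simulations of the same scenarios gave gains of 1 to 2, 3 to 3.5 and 7 to 9 points. About 1 to 8 points is a fair summary.

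**5. Odds-ratio scale.** Unadjusted, the log odds ratio is ln(0.560/0.440) − ln(0.424/0.576) = 0.548, with SE √[1/(123 × 0.2464) + 1/(123 × 0.2442)] = 0.257 and ratio 2.13. With parity OR 5, the common within-parity log odds ratio is 0.640. Combining the two strata (61.5 women per arm in each) by inverse variance gives SE 0.280 and ratio 2.29. Power rises because the conditional effect is larger; its standard error rises too. The narrower interval appears on the risk-difference scale (SE ratio 0.926 in the table).

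**6. Week-38 presentation.** The document gives no strength of association with the covariates. On the risk-difference scale the SE falls by the factor √(1 − R²): 0.5%, 1.0%, 2.5% and 5.1% for assumed R² of 0.01, 0.02, 0.05 and 0.10.

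**The case against.** The strongest reply is that this rests on what a condensed article leaves out. Adjustment of secondary outcomes is nowhere ruled out, and a full protocol or analysis plan that is not shown may provide it. Caesarean section is a research question and a recorded birth variable, but it is not in the opening list of secondary outcomes. The gain is small unless parity is strongly prognostic, and every input except 123 per arm is assumed. All of this stands. It lowers the priority but does not remove the point, because the article sets out both methods and opens the adjusted one with an express restriction to the primary outcome.

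A reader might infer more, and the document does not support it:

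- **That the secondary comparisons are biased or invalid.** They are not. Randomisation protects the unadjusted tests, whose type I error already allows for chance imbalance. The primary outcome also gets bivariate tests and a group-only model, so like-for-like unadjusted results will exist.
- **That missing covariates explain the low caesarean power.** It comes from the assumed effect size; adjustment only moves it from about 57% to 59–64%.
- **That the first-session heart-rate readings are wasted.** The Secondary outcomes section lists "maternal heartbeat prior to the stimulus; foetal heartbeat prior to the stimulus; maternal heartbeat at 5 minutes after the stimulus" and the matching foetal value. No section names a test on the post-stimulus value alone, and a within-woman change is not excluded. A 29% cut in SE at an assumed correlation of 0.7 (1 − √(1 − 0.7²)) would apply only against such a post-only test. Against a change score the SE ratio is √((1 + 0.7)/2) = 0.922, about an 8% cut. There is no defect to report here.

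**Conclusion.** The point holds as a low-priority improvement. As written, the fixed-covariate model belongs to the primary outcome, and caesarean section and week-38 presentation have only an unadjusted route. For caesarean section this forgoes about 1 to 8 points of power. That figure rests on assumed rates of 56% versus 42%, a half-nulliparous sample, a parity odds ratio of 2 to 5, and the planned 25% loss applying equally to this outcome. For week 38 the gain cannot be sized from the document and is probably small. For both outcomes it is a gain in power, or in precision of a risk difference, and not a narrower odds-ratio interval. The primary analysis, the sample size of 492 and control of type I error are untouched.

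**What to change.** In the Statistical analysis section, after the primary-outcome model, add that the same logistic model will be fitted to caesarean section and to cephalic presentation at week 38. It should use only the three fixed baseline covariates, not the data-driven additions, with usual care as reference. Keep the bivariate tests as supporting analyses. Preferably also report, for each, a risk difference standardised over the covariates, and state that the adjusted odds ratio is conditional. If a full protocol or analysis plan already says this, a cross-reference is enough.

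The cost is a few lines of text and code. All the variables are already recorded, and the wording is best settled before the half-sample intermediate analysis.
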